#### Lower extremity functional behavior measurement

Following the ankle ROM tests, all subjects will receive a measurement of lower extremity functional behavior involving a star balance excursion test (SBET) conducted on a single limb. The SBET is a clinical test of dynamic balance.[32] Subjects will assume unilateral stance in the center of a grid marked circumferentially in 45-degree increments. After a learning trial consisting of 6 repetitions in each of the 8 test directions[33], subjects will complete 3 repetitions of single limb squat reach. Two trials will be completed: 1 trial each with the subject standing on the affected and unaffected limbs. Test directions include anterior, lateral, anterolateral, posterolateral, posterior, medial, anteromedial, and posteromedial. The evaluating therapist will record the distance achieved between the stance toe and the contacting portion of the reaching extremity for 3 repetitions in each direction. Fifteen seconds of rest will be provided between trials. Repetitions will be excluded if the subject (1) is unable to maintain weightbearing during the trial; (2) lifts the stance foot; (3) loses balance; or (4) does not maintain the hold or start positions for 1 second. This test demonstrates good reliability (ICC = .67–.97), and demonstrates discriminative validity between non-disabled individuals and patients with chronic ankle instability.[32,34]

### Intervention

Subjects will be randomized into 3 groups after pre-participation screening is completed, informed consent is obtained, and baseline measures are recorded. The first group (n = 9) will receive an HVLA procedure directed to the talocrural joint (Figure 3). With the subject in a seated position on a treatment table and the lower extremity of interest stabilized to the table with a belt, a standardized licensed physical therapy (treating therapist) will grasp the foot of interested with the thenar eminences on the foot's plantar surface. A thrust will be delivered parallel to the long axis of the subject's lower leg after the treating therapist induces passive ankle dorsiflexion to end range. The second group (n = 9) will receive a slow procedure directed to the talocrural joint. Traction will be delivered to the talocrural joint at the treating therapist's second perception of tissue resistance in 3 bouts of 30-second holds, separated by 10 seconds of rest. The third group (n = 9) will receive the manual therapy control intervention. This will consist of the same patient and clinician preparation for the mobilization/manipulation techniques. However, the treating therapist will simply maintain passive DF ROM for the duration of 1 deep inhalation and exhalation by the subject rather than induce an iatrogenic force.

**Figure 3 F3:**
[figure not shown]
**Ankle high-velocity low-amplitude, slow velocity, and control interventions under study**. With the subject in a supine position on a treatment table and the lower extremity of interest stabilized to the table with a belt (A), the treating investigator will grasp the foot of interested with the thenar eminences on the foot's plantar surface (B) and induce passive dorsiflexion to end range (B; open arrow). Iatrogenic force will be provided along the long axis of the tibia in the intervention groups. (B; hatched line) In the control group, the treating investigator will maintain passive dorsiflexion (B; open arrow) for the duration of 1 deep inhalation and exhalation by the subject rather than induce an iatrogenic force.

### Post-intervention testing

Immediately following intervention, subjects will receive a final administration of ankle ROM tests, lower extremity functional behavior test, TMS, and H-reflex measurements. After post-intervention testing, subjects will be discharged from the study.

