### Research Design

Subjects each begin with pre-intervention TMS measures (motor thresholds and input-output curves), ankle range of motion (ROM) tests, and lower extremity functional behavior tests. Each pre-intervention measurement will be taken a total of 2 times with a 30 minute rest break between measurements. Subjects will then be randomized into 1 of 3 comparison groups, each to receive a different manual therapy intervention. Immediately following the intervention, subjects will receive post-intervention TMS measures, ankle ROM tests, and lower extremity functional behavior tests, identical to the pre-intervention assessments.

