#### Ankle range of motion (ROM) measurement

Following the second TMS MT measurement, all subjects will receive 2 different ankle ROM measurements. In the first measurement, subjects will lay prone on a padded table. A single blinded and standardized examiner will measure ankle dorsiflexion ROM with the knee fully extended and then flexed to 90 degrees using a 15.24 cm goniometer in a standard manner.[19] This measurement of ankle ROM demonstrates strong test-retest reliability with knee both flexed (ICC = .97) and extended (ICC = .98).[19] A knee to wall measurement also will be taken.[31] Standing with hand support on the wall, with affected lower extremity anterior and the unaffected lower extremity posterior. Subjects were required to move the knee directly forward to a vertical line on the wall. No attempt will be made to control the height of the medial longitudinal arch during this measurement. For subjects who are unable to touch their knee to the wall (1), the distance from the wall to the anterior aspect of the knee will be measured and recorded in centimeters as a negative value. Subjects who can touch the knee to the wall will move the foot back until the knee could just touch the wall (2). The distance from the wall to the great toe will be recorded in centimeters as a positive value. The knee to wall measurement of ankle ROM also demonstrates strong test-retest reliability (ICC = .97).[31]

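### The post-intervention tests are listed in two different orders, one of which puts TMS after a further balance-test bout that baseline TMS did not follow

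*Protocol article*

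**What the plan says.** Four places in the protocol article bear on the order of testing.

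- **Research Design, baseline.** "Subjects each begin with pre-intervention TMS measures (motor thresholds and input-output curves), ankle range of motion (ROM) tests, and lower extremity functional behavior tests". It adds: "Each pre-intervention measurement will be taken a total of 2 times with a 30 minute rest break between measurements".
- **Research Design, post-intervention.** Straight after the intervention, "subjects will receive post-intervention TMS measures, ankle ROM tests, and lower extremity functional behavior tests, identical to the pre-intervention assessments". The H-reflex is not mentioned here.
- **ROM and functional behavior sections (baseline).** These use explicit words of sequence: "Following the second TMS MT measurement, all subjects will receive 2 different ankle ROM measurements" and "Following the ankle ROM tests, all subjects will receive a measurement of lower extremity functional behavior".
- **Post-intervention testing.** "Immediately following intervention, subjects will receive a final administration of ankle ROM tests, lower extremity functional behavior test, TMS, and H-reflex measurements".

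The pre/post comparison of TMS is central to the study. The Motor threshold section defines altered excitability as pre-to-post change in the MEP and silent-period curves. Data Analysis tests pre/post differences in those data, reports main effects when no interaction is significant, and correlates TMS variables with SBET and ROM. It also treats a TMS change with an unchanged H/M ratio as central in origin.

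**The concern.** Research Design and Post-intervention testing cannot both be the running order. The first keeps the baseline sequence; the second reverses it. Staff following one section would test differently from staff following the other.

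If the second is followed, each subject's post-intervention TMS comes after ROM testing and a fresh SBET bout, and starts later after the intervention. Baseline TMS had neither feature. Four planned uses of the data are then exposed:

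1. **Within-group pre/post change and the time main effect** would contain whatever the reaching and the delay do to excitability.
2. **The minimum detectable change** comes from two baseline TMS measurements that, by the ROM section, both precede the SBET. Their variability does not reflect this exercise.
3. **The central attribution** would give a TMS change caused by reaching the same label as one caused by the procedure.
4. **The TMS-SBET correlation** (aim 3) could reflect an effect of reaching effort on TMS, not of excitability on function.

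**Working it through.** The plan gives no figure for an order effect. Its only power figure (over 80% for lateral SBET, 9 per group, d = 1.47) reproduces as 83.3% by noncentral t with 16 df, assuming two-sided 5%. It does not depend on test order.

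**Step 1. The sequences side by side.**

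| Occasion | Source | Order |
|---|---|---|
| Baseline | ROM and functional behavior sections | TMS (both measurements), ROM, SBET |
| Post | Research Design | TMS, ROM, SBET |
| Post | Post-intervention testing | ROM, SBET, TMS, H-reflex |

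Only the baseline row rests on words of sequence; the two post rows are lists. The second list is the reverse of baseline for TMS.

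**Step 2. Exercise inserted before TMS under the second list.** The functional behavior section gives 3 test repetitions, 8 directions and 2 stance limbs: 3 x 8 x 2 = 48 reaches, of which 3 x 8 = 24 are in stance on the affected limb. If the learning trial (6 x 8 = 48) is repeated once, the total is 48 + 48 = 96. The document does not say whether it is repeated.

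**Step 3. Delay inserted.** Time per reach is not given. Assuming 2 to 10 s:
- 48 reaches: 48 x 2 / 60 = 1.6 min to 48 x 10 / 60 = 8 min
- 96 reaches: 96 x 2 / 60 = 3.2 min to 96 x 10 / 60 = 16 min

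ROM time and rests come on top.

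**Step 4. Delay the other way, if TMS goes first.** The MEP input-output section gives 95% to 140% of threshold in 5% steps (10 levels), 8 stimuli, 2 conditions, 5-10 s apart: 10 x 8 x 2 = 160 pulses, or 13.3 to 26.7 min. If the two muscles are stimulated separately, 320 pulses take 26.7 to 53.3 min. ROM and SBET would wait that long.

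**Step 5. What a common order effect does to the tests.** Simulation: 20,000 runs, 9 per group, change scores normal with SD 1, no treatment effect, and the same shift added in each arm. The within-group test is t = mean change / (SD / 3), two-sided 5%, 8 df. The between-group test is a two-sample t-test on change.

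| Shift (SD of change, assumed) | Within-group rejection | Between-group rejection |
|---|---|---|
| 0 | 5.0% | 4.8% |
| 0.5 | 26.1% | 5.1% |
| 1.0 | 75.1% | 5.3% |

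The within-group column applies if the planned t-tests compare pre with post inside an arm; the wording of Data Analysis leaves that open. The time main effect is exposed in the same way.

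**The case against.** **The lists may not be running orders.** Both post-intervention sentences are comma lists, and the claim that the assessments are identical may refer to content, not sequence. The flow diagram (Figure 1) is not available here and may settle the order. This stands: the certain finding is conflicting text, and the bias follows only if the Post-intervention testing list is used as a schedule.

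**The control arm protects the main comparison.** All three arms follow the same sequence, so an additive order effect common to them cancels, as Step 5 shows. A reader might infer that differences between arms are biased, for instance because an arm that gains range reaches further and this alters its TMS result. The document offers no figure or evidence for that route. Two things would not cancel: fading of a short-lived effect during the delay, and an order effect that depends on treatment.

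**Changing the order does not remove all exercise.** If TMS goes first after the intervention, the baseline SBET still lies between baseline and post TMS. This stands.

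**TMS first is not self-evidently better.** The study is powered on the SBET, and Step 4 shows that TMS first delays it. No passage gives the duration of either effect, so a reader should not infer that TMS must lead.

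**The H-reflex delay is a separate matter.** A reader might blame the list order for an H-reflex taken half an hour after the intervention. Most of such a delay would come from the TMS pulse count, and it would persist wherever the H-reflex follows TMS.

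**Conclusion.** The point holds as an inconsistency in stated test order with a definite consequence if one of the two lists is followed. Under the Post-intervention testing list, post TMS follows ROM and at least 48 extra test reaches, and the within-subject uses of TMS listed above absorb an order, exercise and delay effect that the two baseline TMS measurements do not capture. The document does not give the size or direction of that effect; the 26% and 75% rejection rates are illustrations at assumed shifts of 0.5 and 1.0 SD of change.

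The randomised comparison between arms is not shown to be biased. It is sound if the order effect is additive and common to all arms, and exposed only to dilution or an interaction with treatment. No sample-size figure changes.

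The conclusion assumes that both baseline TMS measurements precede the SBET, as the ROM section says. If Research Design instead means two complete baseline cycles, the second baseline TMS would follow one SBET bout and the point about minimum detectable change weakens, but the stated sequence becomes less clear still.

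**What to change.** Reconcile Research Design, the ROM section, the functional behavior section and Post-intervention testing (and Figure 1, if it shows an order) into one stated sequence. Give the H-reflex a place in it. Use that sequence unchanged at baseline 1, baseline 2 and post-intervention in all three arms, and state whether the SBET learning trial is repeated. Record the clock time from intervention to the start of each test.

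Either TMS-first or ROM/SBET-first is acceptable if it is the same throughout. Stating one order removes the pre/post mismatch. It does not remove all exercise: with TMS first, the extra bout ahead of post TMS goes, but the baseline SBET still separates baseline from post TMS, and the report should say so.

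The cost is schedule wording and a time log. Whichever block goes second starts later after the intervention, by roughly the times in Steps 3 and 4, but that is already true under either current list. It needs settling before testing starts, because data collected in mixed or reversed order cannot be repaired afterwards.

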### Data Analysis

#### TMS measurements

All TMS/EMG data will be analyzed off-line with a customized MATLAB (Mathworks, MA, USA) software tool for analysis of time-series data (dataWizard[35]). Each TMS trial will be analyzed for both MEP and cortical silent period (CSP) duration. At low intensities that did not create a MEP, the maximal peak-to-peak envelope within the time window for typical MEPs will be recorded as the MEP value for that trial. The 8 MEPs occurring at each level of intensity will be averaged. The CSP duration will be defined as the time between TMS and the first return of rectified EMG activity of at least 50% of pre-TMS background activity following a period of sustained silence. The CSP duration will be calculated relative to TMS onset because at lower intensities MEPs often will be absent while CSPs can be detected. When no CSP can be discerned, CSP duration will be marked as 0 msec. Eight CSP duration values will be averaged for each subject. The relationship between average MEP amplitude and CSP data (output) and TMS intensity (input) will be fitted to a sigmoid curve.[29,36] These sigmoid functions will then be characterized by 3 parameters: maximal amplitude, maximal slope, and the midpoint intensity where amplitude is half maximum. The ratio of the largest H and M wave amplitudes also will be calculated (H/M ratio). If the ratio remains the same pre and post ankle thrust then any change in corticomotor excitability assessed through TMS would be considered centrally mediated.

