## Methods/Design

### Subjects

Subjects with post-acute ankle sprains (n = 27) will be enrolled into the study. Inclusion criteria include (i) subject age between 18–60 years, (ii) onset of ankle sprain at least 2 weeks prior to enrollment, (iii) Foot and Ankle Ability Measure Activity of Daily Living subscale score >20%, and (iv) ankle dorsiflexion range of motion limitation greater than 2 standard deviations from published values.[19] Exclusion criteria include (i) assisted ambulation (eg, cane or crutches); (ii) inability to bear weight through the affected extremity immediately after injury; (iii) tenderness to palpation of the medial and lateral malleolar zones, styloid process of the 5th metatarsal, and navicular[20]; (iv) positive anterior drawer or talar tilt dimple test suggesting ligamentous laxity [21-23]; (v) volume of the affected limb greater than 10% of the unaffected limb per water displacement volumetry[24]; (vi) previous history of ligament or bony reconstructive surgery to the ankle and foot; (vii) concomitant injury to other lower extremity joints; and (viii) medical conditions that serve as contraindications to mobilization/manipulation and transcranial magnetic stimulation, such as presence of pacemaker, metal in head, pregnancy, neurological disorders, recent use of stimulants or medications known to lower seizure threshold, and personal or family history of seizures.[25,26]

A total of 27 subjects will be recruited for this study (n = 9 per group). This sample size will provide >80% statistical power to detect differences in lateral star balance excursion performance based on an effect size d = 1.47 from Hale and colleagues[27] involving change in SBET score due to an exercise-based rehabilitation program in individuals with ankle sprains. Therefore, this study was powered to detect between-group differences in the selected lower extremity functional behavior following talocrural manipulation, which is thought to be the dependent variable in this study that will demonstrate the greatest intersubject variability.

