#### TMS measurement

A single-pulse magnetic stimulator (Magstim 200^2^) will be used to carry out all TMS studies. A Double Cone 110-millimetre (mm) coil that provides sufficient depth of penetration to reliably stimulate cortical representation of ankle musculature will be used in this study. Subjects from each intervention group will undergo TMS testing both pre- and post-intervention. The primary motor cortex of the hemisphere contralateral to the impaired ankle will be tested. The pre-intervention session will consist of (i) identifying optimal coil position ('hot spot') and motor threshold (MT) for the target leg muscles (tibialis anterior and gastrocnemius), (ii) conducting input-output (IO) curve studies of both muscles, (iii) input-output curve studies will be conducted both with the muscles at rest and with the muscles pre-activated (active contraction condition). The pre-activated condition is required to generate cortical silent period data.

Surface EMG electrodes will be attached over tibialis anterior and gastrocnemius. The EMG signal will be filtered with a bandpass of 1–1000 Hz, amplified, and digitized at 2000 Hz. The data will be graphically displayed and stored for later analysis in 600-millisecond (ms) samples beginning 100 ms before TMS onset (custom written MATLAB module for analog-to-digital sampling (dwaq; dataWizard acquisition, [name]). For the active contraction condition the subject will be asked to perform maximal dorsiflexion and maximal plantarflexion against a load cell, with care taken to minimize contribution from other muscle groups at the thigh or pelvis. The largest of three attempts is taken as the maximum voluntary contraction force (MVC).

To determine optimal TMS coil location and orientation, TMS pulses are delivered while the subject contracts the ankle musculature and at an inter-stimulus interval of 5–10 seconds. The coil is initially placed at the vertex and the optimal scalp position for TMS ('hot spot') is determined by moving the coil a few centimetres (cm) in each direction from this position and observing the site at which the largest motor evoked potential (MEP) is produced at supra-threshold intensities. The initial muscle contraction serves to facilitate induction of MEPs and is used to aid in finding the motor hot spot.

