#### H-reflex

In order to determine whether potential changes in TMS-assessed corticospinal excitability pre- and post-intervention are spinally and/or centrally mediated the Hoffmann (H) reflex will be performed. The H reflex is considered the electrical analogue of the tendon stretch reflex. Since it bypasses the effects of gamma motoneurons and muscle spindle discharge, it can be used as a method for assessing spinal reflex excitability in intact human subjects before and after intervention.[30] The H-reflex will be elicited using a Cadwell Sierra Wave EMG Nerve Conduction Device (Cadwell Laboratories, Kennewick, WA, USA) by selective electrical stimulation of the Ia fibers of the posterior tibial nerve at the popliteal fossa. In response to afferent nerve stimulation, H-waves can then be recorded as MEPs using surface EMG electrodes over the soleus muscle. Such stimulation can be accomplished by using slow (less than 1 pulse/second), long-duration (0.5–1 ms) stimuli with gradually increasing stimulation intensity. As stimulator intensity increases, the peak-to-peak H-wave amplitude gets larger and a direct short-latency motor response (M-wave) also begins to develop. The M-wave indicates that orthodromic motor fibres are now being directly stimulated at higher intensities. Finally, at supramaximal intensity stimulation, the H-wave disappears because antidromic motor stimulation completely blocks descending H-reflex conduction, and only the direct M-wave can be observed.

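### An unchanged soleus H/M ratio in nine thrust subjects cannot by itself support calling any TMS change centrally mediated

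*Protocol article*

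**What the plan says.** The H-reflex section of the protocol article gives the reason for the measurement: "In order to determine whether potential changes in TMS-assessed corticospinal excitability pre- and post-intervention are spinally and/or centrally mediated". It then names the recording site: "H-waves can then be recorded as MEPs using surface EMG electrodes over the soleus muscle". The TMS measurement section names different muscles for the cortical measures: "Surface EMG electrodes will be attached over tibialis anterior and gastrocnemius". Motor threshold, MEP and silent-period curves are all taken from those two muscles.

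Under Data Analysis, TMS measurements, the article fixes how the result will be read: "If the ratio remains the same pre and post ankle thrust then any change in corticomotor excitability assessed through TMS would be considered" centrally mediated.

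The Intervention section gives the size of the thrust group: "The first group (n = 9) will receive an HVLA procedure directed to the talocrural joint". The sample size in the Subjects section is justified by lateral star balance excursion alone. The section on functional behavior and ROM measurements names the variables for the pre/post t-tests, and those for reliability and minimum detectable change. The H/M ratio is in neither list.

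**The concern.** The rule turns a null finding into a positive statement about mechanism. It has two weak links.

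- **Muscle.** It covers any TMS change, but the spinal measure comes from a muscle in which TMS responses are not recorded. A larger sample would not cure this.
- **Precision.** With 9 subjects, an H/M ratio that looks unchanged is compatible with a sizeable true change. The less precise the H/M measurement, the more readily the ratio passes as unchanged, so imprecision favours the central reading.

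What is at stake is the interpretation of the TMS results. The Background argues that manual therapy may act above the spinal cord, independently of local spinal circuits, and this rule is the only stated route to that conclusion. The Background also reports H-reflex inhibition after spinal manipulation in several studies, so on the article's own account a real H/M change is plausible.

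**Working it through.** **1. Muscles side by side**

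| TMS muscle | Spinal measure in that muscle | What soleus H/M can say |
|---|---|---|
| Tibialis anterior | none | nothing direct |
| Gastrocnemius | none | proxy from a neighbouring calf muscle |

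The rule's coverage of any change therefore goes beyond the data, most clearly for tibialis anterior.

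**2. The article's own power figure.** Inputs from the Subjects section: 9 per group, d = 1.47, power above 80%. Alpha is not stated; two-sided 0.05 is assumed. Two-sample t-test: noncentrality = d × √(n/2) = 1.47 × √4.5 = 3.12 on 16 df. Power = 83.3% (87.7% by the normal approximation). The figure reproduces, but it concerns a between-group difference in star balance excursion and says nothing about H/M.

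**3. Precision of the H/M change in the thrust group.** The article gives no SD for this change, so results are in units of the SD of the pre-post change.

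95% CI half-width = t(0.975, 8) / √9 = 2.306 / 3 = 0.77 SD.

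**4. Chance of missing a real H/M change.** Assumption: sameness is judged by a paired t-test at two-sided 0.05. Noncentrality = 3 × (true change in SD), on 8 df.

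| True change (SD) | Power | Missed |
|---|---|---|
| 0.3 | 12.5% | 87% |
| 0.5 | 26.3% | 74% |
| 0.8 | 55.9% | 44% |

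Power of 80% is reached only at about 1.07 SD. If all 27 subjects were pooled, the half-width would be 0.40 SD and power at 0.5 SD would be 71%.

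**5. Could 9 subjects show sameness formally?** Two one-sided tests at 0.05, true change zero, by simulation:

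| Margin (SD) | Power at n = 9 | n for 80% power |
|---|---|---|
| 0.5 | 5% | 36 |
| 0.8 | 43% | 15 |
| 1.0 | 72% | 11 |
| 1.1 | 82% | 9 |

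A margin set later in an analysis plan would therefore have to be about 1.1 SD or wider to be workable at this sample size.

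**6. Difference from control (9 against 9).** 95% CI half-width = t(0.975, 16) × √(2/9) = 2.120 × 0.471 = 1.00 SD. Power is 17% at a true difference of 0.5 SD and 36% at 0.8 SD.

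**7. Why the minimum detectable change is not a usable margin.** The usual 95% version is an individual-level limit equal to 1.96 SD of the test-retest difference. Assume the pre-post change has the same SD. For a between-group 90% CI, the half-width is about 1.746 × 0.471 = 0.82, so the estimate need only fall below 1.96 − 0.82 = 1.14. With a true change of 0.5 SD, (1.14 − 0.5) / 0.471 = 1.36, which gives a pass rate of about 91%. The paired version passes about 99% of the time. Such a margin would accept real changes even more readily than a non-significant test does.

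**The case against.** - **The 74% is not the rule's error rate.** This stands. A false central verdict needs a missed H/M change and also a TMS change. The joint rate can be no higher than 74% at a true 0.5 SD change and may be much lower. A reader might infer that the rule goes wrong 74% of the time; the documents do not support that. The significance test is itself an assumption, because the article names none for H/M.
- **Locus is not a headline question.** This stands in part. The three numbered aims are TMS reliability, corticospinal excitability by group, and its relation to function. Locus appears as rationale and as the stated purpose of the H-reflex. This lowers the severity but does not make the inference sound.
- **How sameness is judged belongs in the analysis plan.** A missing margin alone would be no finding. The fault is the stated inference. An analysis plan could add a margin, but step 5 shows that only a wide one is workable with 9 subjects, and no margin resolves the mismatch of muscles.
- **The rule is not confined to the thrust arm.** A reader might infer from the words about ankle thrust that the control comparison has been dropped. The H-reflex section speaks of pre- and post-intervention changes generally, and Post-intervention testing applies the H-reflex to all subjects. The phrase is loose, and that inference is not supported.
- **The article says such changes would be considered central, not proved so.** This is correct, but the sentence still attaches the conclusion to any TMS change without qualification.

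**Conclusion.** The concern holds in limited form, at moderate severity. The stated rule supports no locus conclusion for tibialis anterior and at most a proxy conclusion for gastrocnemius. In the 9 thrust subjects, an H/M ratio that appears unchanged leaves a mean change of up to about 0.77 SD either side of the estimate compatible with the data. Under an assumed paired test at two-sided 0.05, true changes of 0.5 and 0.8 SD would be missed 74% and 44% of the time.

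These figures depend on the assumed test and alpha, on the chosen effect sizes and on the use of SD units, since the article gives no SD for H/M change. The mismatch of muscles depends on none of them. The article's sample-size figure is not in question.

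**What to change.** Replace the sentence under Data Analysis, TMS measurements, with a rule that does the following:

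1. Report the pre-post change in soleus H/M with its confidence interval in each group, and the difference of each treatment group from control with its interval.
2. Report a non-significant change as no change in soleus H/M detected, not as proof of central mediation.
3. Make a non-spinal statement only if the interval excludes a spinal change that was judged relevant and fixed in advance on the scale of a group mean. Do not use the individual-level minimum detectable change for this. The section on functional behavior and ROM measurements plans that quantity for MEP/CSP only, and Research Design does not list the H-reflex among the measures taken twice at baseline.
4. Otherwise report the locus as undetermined.
5. Limit any locus statement to the calf muscles and make none for tibialis anterior.

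This changes wording and analysis only; no extra subjects or visits are needed. The cost is that the locus will often be reported as undetermined, the more so against control, where the 95% half-width is 1.00 SD.
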